## Abstract

**Background:**

Therapeutic hypothermia reduces death and disability after moderate or severe neonatal encephalopathy in high-income countries and is used as standard therapy in these settings. However, the safety and efficacy of cooling therapy in low- and middle-income countries (LMICs), where 99% of the disease burden occurs, remains unclear. We will examine whether whole body cooling reduces death or neurodisability at 18–22 months after neonatal encephalopathy, in LMICs.

**Methods:**

We will randomly allocate 408 term or near-term babies (aged ≤ 6 h) with moderate or severe neonatal encephalopathy admitted to public sector neonatal units in LMIC countries (India, Bangladesh or Sri Lanka), to either usual care alone or whole-body cooling with usual care. Babies allocated to the cooling arm will have core body temperature maintained at 33.5 °C using a servo-controlled cooling device for 72 h, followed by re-warming at 0.5 °C per hour. All babies will have detailed infection screening at the time of recruitment and 3 Telsa cerebral magnetic resonance imaging and spectroscopy at 1–2 weeks after birth. Our primary endpoint is death or moderate or severe disability at the age of 18 months.

**Discussion:**

Upon completion, HELIX will be the largest cooling trial in neonatal encephalopathy and will provide a definitive answer regarding the safety and efficacy of cooling therapy for neonatal encephalopathy in LMICs. The trial will also provide important data about the influence of co-existent perinatal infection on the efficacy of hypothermic neuroprotection.

**Trial registration:**

ClinicalTrials.gov, NCT02387385. Registered on 27 February 2015.

**Electronic supplementary material:**

The online version of this article (doi:10.1186/s13063-017-2165-3) contains supplementary material, which is available to authorized users.

## Background

Every year, approximately one million babies die in low- and middle-income countries (LMIC) due to neonatal encephalopathy – a condition arising from an unexpected lack of cerebral blood flow and oxygen supply to the fetal brain at the time of birth [1]. Approximately one-third of infants with moderate or severe encephalopathy will die during the newborn period and up to three-quarters of survivors will develop long-term neurodisability [2, 3]. Until recently, there was no effective treatment for this condition and the management was limited to supportive care.

Several high-quality cooling trials have been conducted in high-income countries in the past decade [4–6]. The meta-analyses of these trials have convincingly demonstrated that selective head or whole-body cooling, along with optimal tertiary intensive care, reduces mortality (risk ratio [RR] 0.8; 95% confidence interval [CI] 0.7–0.9; *p* = 0.005) and improves survival with normal neurological outcome (RR 1.5; 95% CI 1.2–1.9; *p* < 0.001) after neonatal encephalopathy in these settings [7, 8]. The protective effect of cooling persists into later childhood [9, 10]. Whole-body cooling is now widely used as a standard therapy for encephalopathy in the UK and other high-income countries [11].

The safety and efficacy data on cooling therapy from high-income cooling trials cannot be extrapolated to LMICs, due to differences in population co-morbidities, particularly co-existent perinatal infection, growth restriction and meconium aspiration syndrome, and lack advanced cardio-respiratory intensive care facilities [12]. Preclinical data suggest that the brain injury is worse and the neuroprotective effect of hypothermia in neonatal encephalopathy is lost in the presence of co-existent infection, particularly with gram-negative organisms [13].

We systematically reviewed the published literature on the safety and efficacy of cooling therapy for neonatal encephalopathy due to hypoxia-ischemia in LMICs [14]. All published studies were small and/or of poor quality. Two studies reported increased mortality with cooling [15, 16]. A meta-analysis of all these trials showed a trend towards reduced mortality; however, this was not statistically significant (RR 0.74; 95% CI 0.4–1.3). More importantly, the CIs were wide and therefore significant benefits or harm could not be excluded. There were no data on long-term neurological follow-up after cooling therapy [14]. Thus, before cooling therapy is widely used as standard care therapy in LMICs, safety and efficacy data from adequately powered clinical trials are required.

### Aims

#### Primary

To examine whether whole-body cooling to 33.5 °C, initiated within 6 h of birth and continued for 72 h, reduces death or moderate or severe neurodisability at 18–22 months after neonatal encephalopathy, in LMICs.

#### Secondary

To examine if whole-body cooling reduces mortality at hospital discharge and at 18–22 months after neonatal encephalopathyTo examine if whole-body cooling reduces moderate or severe neurodisability at 18–22 months in survivors after neonatal encephalopathyTo examine if whole-body cooling reduces brain injury on magnetic resonance imaging (MRI) and spectroscopy performed during the neonatal period

## Methods

This is a multi-country two arm unblinded pragmatic randomised controlled trial of whole-body cooling along with usual supportive care vs. usual care alone. We plan to recruit 408 babies with moderate or severe neonatal encephalopathy from public sector neonatal units in LMICs over a three-year period. We anticipate approximately 1200 babies will be screened for eligibility to achieve the required target.

The treatment duration (cooling therapy) is 72 h; however, the temperature of all recruited babies will be monitored during the first week after birth. Any temperature rise > 37.5 °C will be actively treated, both in the cooling and usual care arms, as fever increases brain injury and adverse outcomes after neonatal encephalopathy. The neurological outcomes will be assessed at 18–22 months of age. The trial duration will be five years, consisting of a staggered start-up period, 36 months of recruitment followed by a further 18 months of follow-up, and a final five months for data analysis and write-up.

Before the start of recruitment, the local clinical staff at the recruiting centres will have an intensive training on all aspects of the trial and research governance. All staff involved in the study will be required to maintain an up-to-date ICH-GCP certification.

### Inclusion criteria

To ensure wider applicability of the trial intervention, we will use exclusive clinical criteria for selection of at risk infants. Although blood gas analysis and amplitude integrated electroencephalogram may be performed as a part of the clinical care, they will not form part of the eligibility criteria, as these investigations are not widely available in LMICs. Furthermore, accurate Apgar scores are often not available when babies are born at home or in other hospitals and then transferred to the recruiting centres, and often not collected beyond 5 min after birth. Hence, the inclusion criteria from the high-income country cooling trials are inappropriate for LMICs.

Therefore, our inclusion criteria are primarily based on a structured neurological examination using modified Sarnat staging.

Our preliminary data have shown that the HELIX inclusion criteria will identify most infants at high risk of adverse outcomes, without including infants with milder encephalopathy. To be eligible for recruitment, all three criteria below must be met:age ≤ 6 h, birthweight ≥ 1.8 kg, gestation ≥ 36 weeks (based on reported last menstrual period or ultrasound);need for continued resuscitation at 5 min of age and/or 5-min Apgar score < 6 (for babies born at hospital) or lack of crying by 5 min of age (for babies born at home);Evidence of moderate or severe encephalopathy at < 6 h of age on a structured clinical examination based on modified Sarnat staging (Table 1).

**Table 1 Tab1:** Modified Sarnat scale for clinical encephalopathy staging

Categories (total 6)	Signs of neonatal encephalopathy (NE) in each category			
	Normal	Mild NE	Moderate NE	Severe NE
1. Level of consciousness				
	Alert, responsive to external stimuli (state dependent, e.g. post feeds)	Hyper-alert, has a stare, jitteriness, high-pitched cry, exaggerated responds to minimal stimuli, inconsolable	Lethargic	Stupor/coma
2. Spontaneous activity				
	Changes position when awake	Normal or decreased	Decreased activity	No activity
3. Posture				
	Predominantly flexed when quiet	Mild flexion of distal joints (fingers, wrist usually)	Moderate flexion of distal joint, complete extension	Decerebrate
4. Tone				
	Strong flexor tone in all extremities + strong flexor hip tone	Normal or slightly increased peripheral tone	Hypotonia (focal or general) or hypertonia	Flaccid Rigid
5. Primitive reflexes (circle only the highest level in each sign; the maximum score is only 1 in any one category)				
Suck	Strong, easily illicit	Weak, poor	Weak but has a bite	Absent
Moro	Complete	Partial response, low threshold to illicit	Incomplete	Absent
6. Autonomic system (circle only the highest level in each sign; the maximum score is only 1 in any one category)				
Pupils	In dark: 2.5–4.5 mm; in light: 1.5–2.5 mm	Mydriasis	Constricted	Deviation/dilated/non-reactive to light
Heart rate	100–160 bpm	Tachycardia (HR > 160)	Bradycardia (HR < 100)	Variable HR
Respiration	Regular respirations	Hyperventilation (RR > 60/min)	Periodic breathing	Apnoea or requires ventilator
Total score				

The level of encephalopathy will be assigned based on which level of signs (moderate or severe) predominates among the six categories. If moderate and severe signs are equally distributed, the designation is then based on the highest level in Category #1: The level of consciousness. If the level of consciousness is equal, then designation of the NE stage is based on the tone (Category #4). An infant who has seizures will be moderate or severe NE, depending on the neurologic exam. Seizure with normal or mild NE or moderate NE on neurologic exam will be ‘Moderate NE’. Seizure with severe NE will be ‘Severe NE’

### Exclusion criteria

Absent heart rate at 10 min of age despite adequate resuscitation or imminent deathMajor life-threatening congenital malformationsMigrant family or parents unable/unlikely to come back for follow-up at 18 months (expected to be less than 5% of eligible population)

### Outcome measures

#### Primary outcome measure

Severe disability was defined as any of the following: a Bayley III [17] cognitive score < 70; a Gross Motor Function Classification System (GMFCS) level of 3–5 [18]; blindness; or profound hearing loss (inability to understand commands despite amplification).

Moderate disability was defined as a Bayley III cognitive score of 70–84 and either a GMFCS level of 2, seizure disorder or a hearing deficit requiring amplification to understand commands.

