### Follow-up and neurological assessments

The recruiting centres will maintain regular (3–6 months) telephone contact with parents to minimise attrition. The following information will be recorded at each contact:general health status of the baby;any change in home address or telephone number.

Each recruiting centre will have a dedicated and experienced neurodevelopmental paediatrician trained in Bayley Scales of Infant Development (Version III), who will assess the babies aged 18–22 months, masked to the allocation. Inter-observer variability will be addressed and corrected before the start of assessments, by comparing against a gold standard examiner (RS; Pearson’s trainer for Bayley Scales of Infant Development (Version III). The Bayley scales will be administered in one of the local languages (mother tongue of the child) – Hindi, Marathi, Kannada, Tamil, Malayalam, Singhalese, Telugu or Bangla.

Detailed medical history, neurological examination and Gross Motor Function Classification System assessment will be also obtained during this visit using a pre-defined proforma and then entered into the HELIX trial database.

Severe disability will be defined as any one of the following: Bayley III cognitive composite score < 70; Gross Motor Function Classification System level 3–5; hearing impairment requiring hearing aids/cochlear implant; or blindness.

Moderate disability will be defined as cognitive composite score 70–84 and one or more of the following: Gross Motor Function Classification System level II; hearing impairment with no amplification/cochlear implant; or a persistent seizure disorder.

The examiner will feed back the results of the neurodevelopmental outcome tests to the parents, immediately after the assessment. A copy of this report will be provided to the local principal investigator for clinical management. We will also collect information of various morbidities and medical support required during infancy and obtain detailed anthropometry to assess the nutritional status during the 18-month follow-up visit.

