The sample size is based on being able to detect a clinically significant 30% relative risk reduction in death or moderate/severe disability from 50% in the usual care arm to 35% in the intervention (cooled) arm. Using a two-sided 5% significance level and an 80% power, 183 babies per arm are required. Assuming a loss to follow-up rate of around 10%, this comparison requires 204 babies per group, 408 babies in total, to be recruited. In case the adverse outcomes (death and moderate/severe disability) are higher (~65%) in the usual care arm, then this sample size would provide 94% power to detect a 30% relative risk reduction with cooling.

Each CRF (pdf) will be send to the HELIX trial manager within 48 h of discharge/death and all data queries will be resolved in real time by the HELIX research nurse/data entry person. The CRF will be signed off for completion and entered into the HELIX Redcap database by a dedicated data entry person at Imperial College London. The HELIX trial manager will then forward the trial data to an independent statistician, after masking the allocation (as X and Y) for analysis. The trial statistician will analyse the data for IDMC meetings as per a predefined proforma (masked as A and B), at six-monthly intervals or after recruitment of every 50 cases whichever is earlier. The temperature data will be reported to the IDMC as adherence to target temperature, rather than actual temperatures to prevent unmasking of the IDMC members. The principal investigators will not have access to the trial data before locking, nor will they have any role in the data analysis. The trial CONSORT diagram is given in Fig. 2.

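### Two sections define the hearing component of the primary endpoint incompatibly, so some children are events under one and non-events under the other

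*Protocol article*

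**What the plan says.** The abstract states the endpoint: "Our primary endpoint is death or moderate or severe disability at the age of 18 months". Which survivors count as events therefore depends on how moderate and severe disability are defined. The article defines both, in full, in two places.

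**Outcome measures, Primary outcome measure**
- Severe, hearing criterion: "profound hearing loss (inability to understand commands despite amplification"). It suffices alone.
- Moderate: "a Bayley III cognitive score of 70–84 and either a GMFCS level of 2, seizure disorder or a hearing deficit requiring amplification to understand commands". Hearing counts here only together with the cognitive band.
- The severe definition is repeated in the secondary outcomes under Neurodisability (18–22 months).

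**Follow-up and neurological assessments**
- Severe: "Severe disability will be defined as any one of the following: Bayley III cognitive composite score < 70", with the list going on to "hearing impairment requiring hearing aids/cochlear implant; or blindness". Hearing again suffices alone.
- Moderate: a cognitive score of 70–84 plus at least one further item, the list ending "hearing impairment with no amplification/cochlear implant; or a persistent seizure disorder".

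No sentence gives either section precedence.

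**The concern.** Needing amplification is a moderate criterion in the outcome section and a severe one in the follow-up section. The outcome section grades hearing by whether the child understands commands. The follow-up section grades it by whether a device is needed or used. These are different constructs, so loose paraphrase does not explain the gap.

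The conflict would matter less if it only moved children between moderate and severe, because the composite counts both. It goes further, because the outcome section counts aided hearing loss only within the 70–84 cognitive band, whereas the follow-up section counts it at any score. Two analysts who each follow the article faithfully could therefore report different primary event counts, as well as different counts of severe disability.

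**Working it through.** **1. The plan's own sample size.** Inputs from Statistical methods: event rates "from 50% in the usual care arm to 35% in the intervention (cooled) arm", two-sided 5% level, 80% power, 10% loss.

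- Uncorrected: n = [1.96·√(2·0.425·0.575) + 0.8416·√(0.50·0.50 + 0.35·0.65)]² / 0.15² = 169.3, so 170 per arm.
- With continuity correction: (169.3/4)·[1 + √(1 + 4/(169.3·0.15))]² = 182.4, so 183 per arm, as stated.
- With loss: 183/0.9 = 203.3, so 204 per arm and 408 in total, as stated.

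The calculation reproduces and does not depend on which hearing definition is used.

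**2. The two rule sets side by side.** I crossed three cognitive bands (<70, 70–84, ≥85), three GMFCS bands (0–1, 2, 3–5), four hearing states (none; impaired without amplification; aided and understands commands; aided and does not) and seizure disorder (yes/no). That gives 3 × 3 × 4 × 2 = 72 combinations. Blindness is taken as absent, and impairment without amplification is read as not needing it to understand commands. The rules disagree on 9 combinations, which form three profiles:

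| Profile | Outcome measures | Follow-up section | Primary composite |
|---|---|---|---|
| (a) Cognition ≥85, GMFCS 0–2, aided, understands commands (4 combinations) | Not disabled | Severe | Non-event becomes event |
| (b) Cognition 70–84, GMFCS 0–1, no seizure disorder, impairment without amplification (1) | Not disabled | Moderate | Non-event becomes event |
| (c) Cognition 70–84, GMFCS 0–2, aided, understands commands (4) | Moderate | Severe | Unchanged |

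Profiles (a) and (c) change the severe-disability secondary outcome.

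**3. How many children.** The article gives no rate of hearing impairment, so I assume that 1–5% of survivors have hearing loss that the two sections class differently. Survivors: 2 × 183 = 366 evaluable babies; the Background puts neonatal mortality at about one-third, so 366 × 2/3 = 244.

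| Assumed rate | Children | Share of 366 |
|---|---|---|
| 1% | 2.4 | 0.7 points |
| 3% | 7.3 | 2.0 points |
| 5% | 12.2 | 3.3 points |

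At each assumed rate these are maxima for the composite. Profile (c) is an event under both sections, and so is any child with cognition below 70 or GMFCS 3–5.

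**4. Effect on the comparison.** An equal shift of 3.3 points gives 53.3% against 38.3%. The difference stays at 15 points and the risk ratio moves from 0.35/0.50 = 0.70 to 0.383/0.533 = 0.72.

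Pushing further, to 5% of all babies in each arm, gives 55% against 40%, a risk ratio of 0.73. With power = Φ{[0.15·√183 − 1.96·√(2p̄(1−p̄))] / √(p₁(1−p₁) + p₂(1−p₂))}, uncorrected:
- at 50% against 35%: Φ(0.954) = 83.0%
- at 55% against 40%: Φ(0.924) = 82.2%

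The starting value exceeds 80% only because the 183 was derived with the continuity correction. If the switches were not equal, each child of imbalance between arms would move the difference by 1/183 = 0.5 points.

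**The case against.** The strongest reply is that the effect is small. Few toddlers are likely to fit profile (a) or (b), and the risk ratio and power barely move. That stands, and it rules out presenting this as a loss of power.

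Four stronger readings are tempting, and the article does not support them.

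- **A child with profound loss and no device also changes class.** This does not follow. The outcome section's wording presupposes that amplification was tried. The follow-up section's severe criterion turns on requiring a device, which can cover a child who was never fitted.
- **The outcome section's wording is better because it does not depend on access to a device.** The same wording defeats this, since inability despite amplification is hard to establish without amplification. The article does not show which version is preferable.
- **Up to 3.3 points is a large part of the planned 15-point effect.** The first figure is an upper bound on a shift in the overall event rate, under an assumed prevalence. The second is a difference between arms, which an equal shift leaves unchanged.
- **The definition could be picked to suit the result.** Outcome assessors are masked, the statistician receives allocation under codes, and principal investigators have no data before lock and no part in the analysis. These safeguards limit biased selection. They do not say which definition applies.

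Nor is the conflict explained by the article being a condensed account, because both definitions are written out in full. The follow-up proforma is not shown and may already record enough detail to apply either rule, so it is not itself a defect.

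**Conclusion.** The point holds as an internal inconsistency in the definition of the primary endpoint. With no other qualifying deficit, profiles (a) and (b) cross the primary event line and profile (c) changes only the severe-disability secondary outcome.

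The size is uncertain and probably small: at most about 2–12 children, or 0.7–3.3 points of the overall event rate. This rests on an assumed 1–5% of survivors being affected, one-third mortality and 366 evaluable babies. If switches fall equally on the arms, the risk ratio moves from 0.70 to about 0.72. The case for correction rests on the principle that a confirmatory primary endpoint must give each child one classification, and not on lost power.

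**What to change.** Before outcome data are analysed, choose one hearing criterion for severe disability and one for moderate disability, including how each combines with the cognitive score. State them under Primary outcome measure, and align Neurodisability (18–22 months), Follow-up and neurological assessments and the follow-up proforma to them. The article does not settle which wording should prevail; the trial team must reconcile the sections.

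Derive the disability class centrally from the recorded hearing items, and check that the proforma captures what the chosen rule needs: impairment, device needed, device fitted, and understanding of commands with and without it.

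The cost is a wording amendment and one check of the proforma, with no extra babies or study procedures. It is cheapest before the first 18-month assessment, because items not recorded then may not be recoverable.

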#### Secondary outcome measures

##### Clinical outcomes (before discharge from hospital)

Mortality from any cause before discharge from hospitalMajor intracranial haemorrhage on cranial ultrasoundGastric bleeds (fresh blood > 5 mL from nasogastric tube)Persistent hypotension (mean blood pressure < 25 mmHg despite maximum inotropic support)Pulmonary haemorrhage (copious bloody secretions with clinical deterioration requiring change(s) in ventilatory management)Persistent pulmonary hypertension (severe hypoxemia disproportionate to the severity of lung disease with a significant pre- and post-ductal saturation difference on pulse oximetry)Prolonged blood coagulation requiring blood productsCulture-proven early onset sepsis (isolation/identification of a pathogenic organism from blood and/or cerebrospinal fluid along with clinical evidence of sepsis and elevation of C-reactive protein)Necrotising enterocolitis (abdominal distension, increased gastric aspirates and/or blood in stools, together with abdominal X-ray showing bowel oedema, pneumatosis or pneumoperitoneum, i.e. Bell’s staging 2 or 3)Cardiac arrhythmia requiring therapySevere thrombocytopenia (<25,000)Persistent metabolic acidosis lasting over 12 h after birthRenal failure (anuria > 48 h with azotaemia)Pneumonia (infiltrates on chest X-ray consistent with infection or aspiration)Subcutaneous fat necrosisNeurological examination at dischargeDuration of hospitalisation

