### Adverse events

All known adverse events relating to neonatal encephalopathy and cooling therapy are described in the parent information leaflet and will be part of obtaining the informed research consent, before the start of cooling therapy.

The following clinical events (1–9) occur due to the underlying disease (neonatal encephalopathy). Cooling trials from high-income countries have shown that cooling therapy reduces/does not increase the incidence of many of these clinical events in encephalopathic babies.Death during neonatal period or during infancyBrain injury observed with MRIAdverse neurodevelopmental outcome at 18 months and at childhoodPersistent pulmonary hypertensionMetabolic imbalancesCardiac arrhythmiaRenal failureCoagulopathyGastric bleeds

Cooling therapy may increase the risk of the following adverse events noted in the previous randomised controlled trials.Thrombocytopenia and increased need for platelet transfusionsSubcutaneous fat necrosis

All adverse events are expected to occur within the cooling period (first 72 h) or within 72 h of re-warming. Adverse reactions occurring subsequently (after one week of life), except subcutaneous fat necrosis, will not be considered as intervention related. Subcutaneous fat necrosis may occur several weeks after the therapy.

If an unexpected serious adverse event (SAE) occurs (i.e. an event not mentioned in the above list), it should be reported to the HELIX trial manager within 24 h, using one of the SAE report forms. The HELIX trial manager will ensure that the independent data monitoring committee (IDMC) and the research ethics committee (REC) are informed accordingly.

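### Subcutaneous fat necrosis is counted only up to hospital discharge, although the protocol says it can appear weeks after cooling and still be attributed to it

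*Protocol article*

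**What the plan says.** Under Secondary outcome measures, the protocol article groups 17 items beneath the heading "Clinical outcomes (before discharge from hospital"). Subcutaneous fat necrosis is one of them, and no longer window is attached to it.

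The Adverse events section treats the same condition differently:

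- It introduces a list of two entries with the words "Cooling therapy may increase the risk of the following adverse events noted in the previous randomised controlled trials". One entry is thrombocytopenia with more platelet transfusion; the other is subcutaneous fat necrosis.
- It sets an attribution rule with a single exception: "Adverse reactions occurring subsequently (after one week of life), except subcutaneous fat necrosis, will not be considered as intervention related".
- It gives the reason for that exception: "Subcutaneous fat necrosis may occur several weeks after the therapy".

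On data collected after discharge, the section Follow-up and neurological assessments states: "The recruiting centres will maintain regular (3–6 months) telephone contact with parents to minimise attrition". Two things are recorded at each contact: "general health status of the baby", and any new address or telephone number. At the 18-month visit, morbidities during infancy are collected in general terms, without naming this one.

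**The concern.** The counting window and the onset period stated in the same article do not fit together. The protocol accepts that a case of fat necrosis several weeks after therapy may be due to cooling. Yet a site that applies the outcome definition as written records no event for a baby who develops it at home.

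The safety of cooling in low- and middle-income countries is a stated purpose of the trial, and this is one of only two entries on the list of harms that cooling may increase. An incidence counted to discharge could be read as the full incidence, and a low or zero count would look more reassuring than the data allow.

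**Working it through.** The article gives no figure for this outcome that could be reproduced, so the main check is to set the sections side by side.

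**Where could a case arising after discharge be recorded?**

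| Place in the article | What it covers | Does it capture a late case? |
|---|---|---|
| Secondary outcomes, clinical list | Events up to discharge | No, by its heading |
| Secondary outcomes, Neurodisability (18–22 months) | Mortality, severe disability, microcephaly | No |
| Adverse events, 24-hour SAE report | "If an unexpected serious adverse event (SAE) occurs (i.e. an event not mentioned in the above list") | No; fat necrosis is on the list |
| Follow-up, telephone contacts | General health and contact details | Possibly by chance; not linked to the outcome |
| Follow-up, 18-month visit | Morbidities in general | Possibly by chance; not linked to the outcome |
| Statistical methods, data flow | CRF sent within 48 h of discharge or death | No later return is described |

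No stated route leads from a case after discharge to the outcome.

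**Effect on the comparison.** Let p1 and p0 be the true incidences with cooling and with usual care, and s1 and s0 the shares of cases that appear before discharge.

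- Observed risk ratio = (p1 × s1) / (p0 × s0). If s1 = s0, this equals p1/p0, so there is no bias.
- Observed risk difference with s1 = s0 = s is s × (p1 − p0). With s = 0.5, any true excess is halved.
- Fewer counted events also mean wider confidence intervals.

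**Illustration 1: upper limit when no event is seen.** The 204 babies per arm come from the sample size paragraph. The shares s are assumed.

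- Full capture: 1 − 0.05^(1/204) = 1.46%.
- s = 75%: 1.46% / 0.75 = 1.9%.
- s = 50%: 1.46% / 0.50 = 2.9%.
- s = 30%: 1.46% / 0.30 = 4.9%.

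**Illustration 2: cases lost.** Assume a true incidence of 2% among 204 cooled babies. Expected cases are 204 × 0.02 = 4.1. The counted number is 204 × 0.02 × s, and the chance of counting none is (1 − 0.02 × s)^204.

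| Share before discharge (assumed) | Counted | Lost | Chance of counting none |
|---|---|---|---|
| 100% | 4.1 | 0 | 1.6% |
| 75% | 3.1 | 1.0 | 4.6% |
| 50% | 2.0 | 2.0 | 12.9% |
| 25% | 1.0 | 3.1 | 36.0% |

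Both illustrations treat all 204 babies as at risk throughout. The Background says about one-third of such infants die in the newborn period, so fewer would be at risk after discharge.

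**The case against.** The strongest reply is that this is absent detail rather than conflict. Exempting fat necrosis from the one-week rule suggests that the safety process expects late reports. The telephone contacts and the 18-month history, taken on a pre-defined proforma, might bring cases to light, and the items on those forms belong in the full protocol and CRF. This stands in part: the forms may ask the question, and the article cannot show that they do not. But the article does state an outcome window and an onset period, and these disagree. A form that detected a late case would still leave it outside the outcome as defined.

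A reader might go further and infer that fat necrosis is specific to cooling, so that the lost cases lie almost entirely in the cooled arm and the comparison is biased in favour of cooling. The article does not support this. It says only that cooling may raise the risk, which leaves room for cases under usual care. With equal capture in both arms the expected risk ratio, the planned effect measure for categorical outcomes, is unchanged. Nothing in the article shows that capture would differ.

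A reader might also take from the illustration that the trial would report an upper limit two to three times too low. That ratio merely restates the assumed shares of 50% and 30% (1/0.5 and 1/0.3). A share of 75% gives a factor of 1.3, and the article plans no one-sided limit of this kind.

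**Conclusion.** The inconsistency is real and lies in the text itself. As defined, the outcome excludes cases after discharge of a harm that the protocol says can arise later and can still be attributed to cooling. If such cases occur, absolute incidence and any absolute excess with cooling are understated and precision is lost. Bias in the risk ratio would need a pre-discharge share that differs by arm.

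The size is unknown, since the article gives neither incidence nor length of stay. It cannot be said that cases certainly will be lost, only that any arising after discharge fall outside the definition. The figures above show how much the reading of a low count depends on the unknown share; they are not estimates for this trial.

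The primary outcome, the sample size and the main analysis are unaffected. The point is nevertheless worth correcting, because it concerns one of two listed harms and the correction is cheap.

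**What to change.** Reconcile the secondary outcome list with the Adverse events section:

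1. Take subcutaneous fat necrosis out of the list that ends at discharge, and give it its own stated window extending beyond discharge.
2. Ascertain it in both arms with one identically worded question at the first planned telephone contact. The article gives only a 3–6 month interval for these contacts, so the timing of the first must be fixed.
3. Have site staff ask the question, and keep the answer away from the assessor at 18–22 months. That assessor is masked and contributes to the primary outcome; a question about a harm linked to cooling at that visit could reveal the allocation.
4. Report cases before and after discharge separately.

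The cost is one revised outcome definition and one question on a call already planned. The downside is data quality: parents know the allocation and have been told of the known adverse events, so their reports are less certain and may differ by arm. Identical wording and separate reporting keep that weakness visible but do not remove it.
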